### Generalizability

The study took place in Indigenous reserves in Canada and two rural communities in Tanzania. These communities were rural and remote, had limited access to primary care providers, and, in Tanzania, often had difficulty accessing medication for treatment continuity. In these communities, inconsistent BP measurement and follow-up, as well as poor access to antihypertensive medications, were known to contribute to poorer rates of BP control.

### Statistical Analysis

All patients who receive at least one SMS message and for whom data for one or more follow-up BP reading is available will be included in the efficacy and safety analyses.

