## Methods

### Study Goals

The purpose of this study is to investigate the efficacy of an evidence-based system of SMS messages linked to accurately measured BP in the community. The individual BP measurements are taken by community health workers (CHWs). This innovation allows for transmission of accurate BP measurements from patients in isolated or underserviced populations to health care providers and, subsequently, improvement of patient knowledge about hypertension management. Participants in the Dream-Global study are randomized to receive either SMS messages that are both active and passive, compared with those receiving only passive messages. All messages are derived from the Hypertension Canada Clinical Practice Guidelines and are subsequently modified with community input to make them culturally sensitive and specific in both Canada and Tanzania [25]. The 12 active messages explain the importance of BP control, describe the rational for medical therapy, and, based on the BP reading, may instruct the participant to contact their health care provider for further BP follow-up. The 26 passive messages include health behaviors change advice for diet and exercise. Messages are sent twice weekly, on Monday and Thursday at 11 AM (to avoid holidays). The study is divided into five projects that involve the design, implementation, and then staging of the research program for the successful execution of a randomized controlled trial in both Canada and Tanzania.

*Project 1* is to develop a readiness to participate tool. The tool entails a multidimensional checklist intended to assess community readiness for implementation of a research program for hypertension awareness, treatment, and control. The tool developed was piloted in both Canadian Indigenous and Tanzanian communities participating in the Dream-Global study with evaluation and feedback for validation [24].

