Eligible participants were registered online. At registration, they were randomized electronically to receive active and passive SMS messages or passive only, and their names were then listed on the Dream-Global mobile app on the smartphone used by the Home and Community Care nurse or CHR in their community. BP was measured with the A&D UA-767PBT-C monitor (A&D Medical, San Jose, CA) to test that it was being transmitted properly; an SMS message to the participant’s registered mobile phone, with the BP reading, was the confirmation of transmission. The Home and Community Care nurse and CHR were trained to take three BP readings with this device. The study server was programmed in such a manner that it waits for up to three readings and then sends their mean to the participant’s own phone. Randomization through the study server ensured that participants and study personnel were blind to the allocation.

The baseline BP was defined as the mean of all readings from the A&D device in the first 2 months after randomization. If the average BP was uncontrolled during the first 2 months, the patient was identified as being in the BP lowering study; otherwise, they were followed up for BP screening. BP readings were stored on the central server, and deidentified data were transferred monthly to the data analysis center in Ottawa.

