### Safety Analyses

The primary study safety variable is the overall incidence of adverse events (AEs) between study entry and end. Descriptive summary statistics will be presented for the number and severity of AEs reported by each patient, overall and by individual organ system. The upper limit for the 95% one-sided CI for the incidence of the most frequent AE will be calculated.

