### Knowledge Translation and Engagement

Annual presentations will be made to each community on the study’s progress. At the end of the study, presentations are made to the community leadership, health care providers and participants, and community members through town-hall style meetings. Results will also be summarized in a poster for the communities. Annual presentations are made at the GACD study meeting, at which the other 14 study teams also present their updates.

Requirements of the Dream-Global app.Participants must be registered securely.Participants’ names will only show up on their community health resource’s or community health worker’s Dream-Global smartphone.Blood pressure readings on the A&D Medical monitor would transmit by Bluetooth to the smartphone.Blood pressure readings on the smartphone would be transmitted to the central server.A mean of the readings received by the central server would then be sent to the participant’s own phone (different from the community health worker’s smartphone).The central server will send the mean of the readings to the participant’s health care provider by fax in the form of a letter, based on the information provided at registration (Canada only).The server will be programmed to assess the blood pressure reading as normal or high and, if high for the participants receiving active messages, to advise them to see their health care provider for blood pressure management. In Canada, messages will include the phone number of their health care provider; in Tanzania, messages will include the location and weekdays on which the local blood pressure assessment clinic is running.

Abstracts will be presented at local, national, and international meetings as appropriate, and there will be publications in the peer-reviewed literature documenting the study progress and results. Furthermore, semiannual presentations will be made to Health Canada, specifically for the First Nations and Inuit Health Branch that funds the Home and Community Care health delivery in most First Nations communities. Semiannual progress reports are also submitted to the National Institute for Medical Research Tanzania. 

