### Blood Pressure Control Study and Primary and Secondary Outcomes

For the BP control study, the primary outcome is the difference between the two groups in BP change from baseline to study end (both systolic and diastolic). One year was chosen as a target for BP monitoring to allow for sufficient measurements and to reduce the Hawthorne effect, in which improved BP control from better adherence might occur for the period after study enrolment [34]. To reduce the effect of regression to the mean, the baseline BP was defined as the mean of the BP readings (each mean of three measures) taken with the A&D UA-767PBT-C in the first 2 months after enrolling in the study. The final BP measurement is the mean of the last 2 to 3 measurement days, usually in the last 2 months, to reduce variability from a single set of readings. The secondary outcome is the proportion of participants achieving BP control during the study period.

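### The single analysis set requires a follow-up BP reading even for safety, which conflicts with counting adverse events from study entry; it also conditions efficacy on attendance after randomization

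*Protocol article*

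**What the plan says.** The Statistical Analysis section sets two conditions, "All patients who receive at least one SMS message and for whom data for one or more follow-up BP reading is available", and says that those who meet them "will be included in the efficacy and safety analyses". The article describes no separate safety set and no all-randomized set.

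Under Safety Analyses: "The primary study safety variable is the overall incidence of adverse events (AEs) between study entry and end".

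Three other statements bear on how the set works:

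- Blood Pressure Screening: Canada, on timing: "At registration, they were randomized electronically to receive active and passive SMS messages or passive only".
- The same section, on baseline: "The baseline BP was defined as the mean of all readings from the A&D device in the first 2 months after randomization".
- Blood Pressure Control Study and Primary and Secondary Outcomes, on the endpoint: "The final BP measurement is the mean of the last 2 to 3 measurement days".

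**The concern.** Randomization takes place at registration, so both conditions for entering the analysis are met or failed afterwards. The BP condition is the one that matters. Messages go out twice a week, so most people would be sent one within days, whereas a BP reading exists only if the participant meets the community health resource (CHR), nurse or community health worker who takes it.

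For safety, the rule and the outcome do not fit together. The outcome starts at study entry. The set admits people only once a later BP reading exists. Someone who dies, is hospitalized or withdraws before that reading is not counted at all, in a trial whose primary safety variable is AE incidence.

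For efficacy, a change score does need a later value, so some restriction is understandable. But the comparison then rests on people selected by attendance, nothing based on all randomized participants stands beside it, and the article does not say which readings qualify as follow-up.

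**Working it through.** **1. The plan's own figures.** None is given on this point: no expected loss, AE rate or count of people without a reading. The 97% power in the Sample Size section is a separate matter. It does reproduce: pooled SD √((10.6² + 11²)/2) = 10.80, difference 4.8 mm Hg, 176/1.1729 = 150 effective per arm, two-sided 5% assumed, power 97.1%. By the same formula, the target of 360 gives 95.8% with 10% excluded and 93.6% with 20% excluded. The issue is who is counted, not power.

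**2. Safety rule against safety outcome.** The outcome runs from entry to end. The set needs an SMS and a later BP reading. Take a participant with an AE in week 6 who then leaves. If follow-up means after the 2-month baseline window, that person is outside the set and the AE is lost. The conflict follows from the text and needs no assumption about rates.

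**3. Size of the safety effect (all inputs assumed).** Let d be the share without a follow-up reading, p_r the AE rate in those retained and p_l the rate in those lost.

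- Reported incidence = p_r
- True incidence = (1 − d)·p_r + d·p_l
- Share of participants with an AE who are not counted = d·p_l / true incidence

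With p_r = 10%:

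| d | p_l | True incidence | Reported | Share not counted |
|---|---|---|---|---|
| 5% | 10% | 10.0% | 10% | 5% |
| 10% | 10% | 10.0% | 10% | 10% |
| 10% | 20% | 11.0% | 10% | 18% |
| 20% | 20% | 12.0% | 10% | 33% |
| 20% | 30% | 14.0% | 10% | 43% |

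The error in incidence is d·(p_l − p_r). It is zero when the two rates are equal and changes sign when leavers have fewer recorded events. With d = 10% and p_l = 5%, true incidence is 0.9 × 10% + 0.1 × 5% = 9.5%, and the plan would overstate it.

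**4. What counts as follow-up.** An A&D reading is taken around registration to test transmission, baseline is the mean of A&D readings over the next 2 months, and the final value is the mean of the last 2 to 3 measurement days. If any A&D reading qualifies, few people are lost. But someone who leaves within 2 months then has a final value that can be built from the same readings as the baseline. If only readings after the window qualify, more people are lost. The article does not say which applies.

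**5. Size of the efficacy effect (all inputs assumed).** If those excluded differ from those retained by g mm Hg in BP change, the same in both arms, and the excluded shares are d₁ and d₀, the between-arm difference shifts by (d₀ − d₁)·g.

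- Equal loss: 0, whatever g is.
- 10% v 20%, g = 3 to 8: 0.10 × 3 = 0.3 to 0.10 × 8 = 0.8 mm Hg.
- 5% v 25%, g = 3 to 8: 0.20 × 3 = 0.6 to 0.20 × 8 = 1.6 mm Hg.

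For scale, the Sample Size section treats a difference as small as 2 mm Hg systolic as important.

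**The case against.** Restricting an efficacy set to people with post-baseline data is common, one reading is a low bar, and allocation was concealed from participants and staff. Those points have some force for efficacy. The rule also leaves people in the arm to which they were allocated; it restricts the set and does not regroup it. None of this explains why a safety count should need a BP reading.

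Four stronger readings are tempting and are not supported.

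- *The active messages raise attendance, so inclusion differs by arm.* The Study Goals section says active messages "may instruct the participant to contact their health care provider for further BP follow-up", and the app requirements have the server, "if high for the participants receiving active messages, to advise them to see their health care provider". Both point to the provider. The study BP is taken by the CHR, nurse or health worker, and the Canadian provider only receives the result by fax. An indirect effect is possible but not documented.
- *AE incidence is certainly understated.* That needs more events among leavers. The AEs are those reported by patients, and people who leave early have less time under observation and may report nothing. Adding them to the denominator without ascertainment could lower the incidence.
- *A between-arm AE difference is being hidden.* The Safety Analyses section states no between-arm comparison.
- *The Results show the loss.* The 234 people with at least one set of transmitted readings are a descriptive count. It is not called the analysis set, and the number randomized without a reading is not given.

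**Conclusion.** The point holds. On safety it is a conflict between two stated rules: AEs are to be counted from entry to end, but only in people who later produce a BP reading. The direction of the error depends on the event rate among early leavers, and the document does not allow its size to be estimated. Under the assumed ranges, the error in incidence runs from 0 to 4 percentage points, and 5% to 43% of participants with an AE go uncounted.

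On efficacy it is a weakness and no more. The set is conditioned on attendance after randomization, and follow-up is not tied to the baseline window. Bias arises if loss, or the outcome gap between leavers and stayers, differs by arm. The 0.3 to 1.6 mm Hg illustrations rest wholly on assumed inputs, and equal loss with an equal gap gives none. The plan should be changed on this point, and the safety change is the clearer of the two.

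**What to change.** **Safety.** Define the safety set as all randomized participants sent at least one SMS, regardless of BP data. Count AEs from study entry, and report follow-up time for those who leave early so that short observation is visible.

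**Efficacy.** Analyse participants by allocated arm. State which readings count as follow-up relative to the 2-month baseline window. Report the number randomized and the availability of follow-up BP by arm. Add a sensitivity analysis that includes all randomized participants in the BP lowering study by multiple imputation with delta adjustment, using the screening BP recorded before randomization. A repeated-measures model alone is not enough: with baseline as a covariate, a person with no later reading contributes no outcome and still drops out. Membership of the BP lowering study is itself set from A&D readings after randomization, so the plan must also say how people with no reading in that window are classified; the screening BP is available for this.

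**Cost.** A wording change for the safety set and modest extra analysis for efficacy. The last patient finished in December 2016, so AE ascertainment for early leavers may be incomplete, and this should be reported as a limitation.

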### Efficacy Analyses

The primary efficacy endpoint in this study will be assessed by analysis of variance. Descriptive data will be given, with the mean and standard deviation for continuous data and proportions for ordinal data. Preplanned exploratory subgroup analyses will include analysis by community, sex, diabetes status, phone ownership at baseline, and age. The knowledge gained from the text messages will be assessed by questionnaire at study completion, and results will be compared between the groups.

### Safety Analyses

The primary study safety variable is the overall incidence of adverse events (AEs) between study entry and end. Descriptive summary statistics will be presented for the number and severity of AEs reported by each patient, overall and by individual organ system. The upper limit for the 95% one-sided CI for the incidence of the most frequent AE will be calculated.

### Meta-Analysis

This study is one of the series of clinical trials being undertaken by the Global Alliance on Chronic Disease (GACD). In addition to the study-specific analyses outlined above, study data will become part of a common database for all clinical trials in the GACD hypertension series to perform meta-analyses. These analyses will be defined prospectively and are intended to identify subpopulations and other baseline characteristics of treatment patients that may influence treatment outcomes. Only denominated data will be used. Analysis and dissemination will take into account the principles of shared ownership of research findings held by university-based researchers and community partners as outlined in the research agreements.

### Development of SMS Message Bank

The development of the SMS messages took place through a process of community engagement with Indigenous and Tanzanian communities who were motivated to participate in the research program. Through a series of focus groups and individual interviews with health care providers and people with hypertension, as well as with other community stakeholders, we developed culturally appropriate and acceptable SMS messages through a process that has been published [26].

### Quality Control

The overall procedures for quality assurance of clinical study data follow those of Good Clinical Practice and the principles of ethical research involving the First Nations, Inuit, and Métis People of Canada as put forth in the Tri-Council Policy Statement 2 (TCPS2) [27]. A data safety monitoring board was established for this study to monitor the study annually.

### Ethics Approval

Approval to conduct the study in Canadian and Tanzanian communities was granted by community leadership in each community. Furthermore, in Tanzania, approval consent and advice was also sought from the Kilimanjaro Regional Medical Officer (RMO), the Hai District Medical Officer (DMO), and the National Institute of Medical Research (NIMR), whose ethics board reviewed the protocol.

The study protocol has been approved by local ethics boards, including The Cree Board of Health and Social Services of James Bay, Ontario (July 10, 2013); the Cree Nation of Chisasibi (August 15, 2013); Manitoulin Anishnabek Research Review Committee (October 7, 2013); the National Institute for Medical Research in Dar es Salaam, Tanzania (approved on March 19, 2014); and Northwest Territories Scientific Research License number 15317 (August 8, 2013). It has also been approved by institutional ethics boards, including the University of Calgary (REB13-0573; September 23, 2013); Queen’s University Health Sciences and Affiliated Teaching Hospitals Research Ethics Board, Kingston, Ontario (DMED-1603-13 approved on June 21, 2013); Sunnybrook Research Institute Research Ethics Board, Toronto, Ontario (ID number 053-2013; May 10, 2013); and the National Institute for Medical Research Tanzania (NIMR/HQ/R.8a/Vol.IX/1698).

### Privacy and Cultural Considerations

The study data are housed in a secure central server with appropriate safeguards for data security and backup and appropriate privacy provisions to avoid deidentification of personal data. The study will maintain the principles of Good Clinical Practice and the principles enunciated in the Declaration of Helsinki and the TCPS on ethical conduct for research involving humans [31,32]. This study will adhere to the principles of ownership, control, access, and possession; our group has experience of working within this important framework [33]. The partners already adhere to the principles of the Personal Information Protection and Electronic Documents Act (PIPEDA), and movement of data in this study will be compliant with this act.

### Program Governance

The Dream-Global team was designed to be multidisciplinary and interprofessional, including First Nations community representatives. The research program brings together nationally recognized leaders in clinical practice guidelines’ implementation and clinical trials and research in hypertension, with expertise to work collaboratively with First Nations communities. Decision makers and the multidisciplinary team members were invited to provide letters of support to clarify their roles. A steering committee was developed and tasked with ensuring that proposed intervention strategies were appropriate for the social, cultural, and economic contexts. Annual research meetings provided a forum to share plans with broader team and community members, as well as to receive feedback before implementing plans. Research reports were also developed and presented to the annual GACD research forum, which included oversight from the CIHR.

### Knowledge Translation and Engagement

Annual presentations will be made to each community on the study’s progress. At the end of the study, presentations are made to the community leadership, health care providers and participants, and community members through town-hall style meetings. Results will also be summarized in a poster for the communities. Annual presentations are made at the GACD study meeting, at which the other 14 study teams also present their updates.

Requirements of the Dream-Global app.Participants must be registered securely.Participants’ names will only show up on their community health resource’s or community health worker’s Dream-Global smartphone.Blood pressure readings on the A&D Medical monitor would transmit by Bluetooth to the smartphone.Blood pressure readings on the smartphone would be transmitted to the central server.A mean of the readings received by the central server would then be sent to the participant’s own phone (different from the community health worker’s smartphone).The central server will send the mean of the readings to the participant’s health care provider by fax in the form of a letter, based on the information provided at registration (Canada only).The server will be programmed to assess the blood pressure reading as normal or high and, if high for the participants receiving active messages, to advise them to see their health care provider for blood pressure management. In Canada, messages will include the phone number of their health care provider; in Tanzania, messages will include the location and weekdays on which the local blood pressure assessment clinic is running.

Abstracts will be presented at local, national, and international meetings as appropriate, and there will be publications in the peer-reviewed literature documenting the study progress and results. Furthermore, semiannual presentations will be made to Health Canada, specifically for the First Nations and Inuit Health Branch that funds the Home and Community Care health delivery in most First Nations communities. Semiannual progress reports are also submitted to the National Institute for Medical Research Tanzania. 

Other efforts will be made to present to policy makers and payers and to community leadership to promote sustainability and scalability at the end of the study. Interested parties will be given the chance to read (or have read to them) the information sheet and ask any questions before providing written consent. Copies of the information sheet and consent form will be given to study participants. All personally identifying information will be removed from study documents. Study participants will be identified using a unique alphanumeric number. To track participants, a list linking the name and home address of each person will be maintained in a locked filing cabinet.

